### Confidentiality

Questionnaires and sample collection will be undertaken by medical staff, and confidential information will be maintained. The responsible investigator and other investigators will use de-identified names when conducting intervention and analyzing the data and use ID numbers to match results. When the results of this study are published, no individual information will be disclosed.

During the intervention phase, the online intervention will be based on WeChat, the WeChat ID of participants will use ID numbers to replace personal privacy information to ensure information security. All members of the research team need to sign a confidentiality agreement to ensure data security.

## Discussion

Evidence suggests that approximately 90% of Chinese and over 90% of European adults exhibit at least on unhealthy lifestyle behavior including smoking, alcohol consumption, physical inactivity, unbalanced diet and obesity, with higher prevalence found for adults living in less economically developed areas [2, 65]. These unhealthy lifestyles often cluster and have additive or synergistic effects, increasing the risk of chronic disease and multimorbidity [66]. Recent advances in mHealth provide an appealing and cost-effective approach to intervention targeting the reduction of unhealthy lifestyles. To date, only a few mHealth studies using multiple-level lifestyle interventions at multi-levels have been conducted in community-based population, all in the USA [24, 25, 67]. So far respective studies in Chinese community residents have not been reported.

The 3SLIFE trial aims to provide a multi-level theoretical framework for mhealth interventions to develop and maintain multi-dimensional healthy lifestyles in Chinese community residents. Several strength warrant mentioning: First, since lifestyles are often clustered, and in additive or synergistic manner increase the risk of multiple chronic diseases, a multi-dimensional healthy lifestyle intervention, which considers the five main unhealthy lifestyles as suggested by previous large-sample size studies, may be more conducive to overall and sustained health outcomes [37, 68, 69]. Second, the strategies of 3SLIFE will be guided by socioecological model and supported by multi-dimensional empowerment approach, which may overcome the shortcomings of both approaches when taken alone, that is lack of an agency dimension in the socioecological model and lack of a clear multi-level environmental dimension in the empowerment approach. Third, several approaches based on multi-dimensional empowerment will be used to promote self-management-oriented lifestyle changes, such as participants’ voluntarily documentation of their daily lifestyle in WeChat groups, and documentation encouraged by family members or medical staff, which will determine the mHealth adoption and utilization as well as lifestyle changes and sustainability. Fourth, the strategies of 3SLIFE will combine online and offline approaches for lifestyle intervention, which may help participants to become more familiar with smart devices and social media apps and increase trust between participants and medical staff. Fifth, this study will conduct a 6-month follow-up, to evaluate sustainability of intervention effects.

This study has the following limitations we are aware of at this point. First, although smartphones have a high coverage rate in China, some people (such as the elderly) may not be able to use them well, which may hinder the implementation and reduce the effectiveness of mHealth interventions. For example, the present study plans to use the apps WeChat and Tiktok as information resource transmission carrier, which may not be the most attractive tools for older people. However, offline interventions will include instructions on the use of these apps for promoting lifestyle changes. Second, for our primary outcome (lifestyles) and secondary outcomes (such as cognition), we mainly use questionnaire indicators, which may be subject to recall bias and socially desirable answer patterns. However, for some indicators prone to recall bias, we will provide documentation records for participants to help recall their lifestyles. Moreover, all group managers will receive standard investigation training (e.g., using sensitive and appropriate language when speaking about healthy lifestyles and chronic disease) and face to face offline investigation will be conducted in a private room. Third, due to the lack of balanced stratification, comparative analyses between subgroups may not be suitable if the sample size of each group is insufficient across groups (e.g., compare specific lifestyle factors across different types of chronic medical conditions).

Despite these limitations, the 3SLIFE trial presents an initial attempt at systematically promoting evidence-based community health promotion in China and is an important first step towards improved public health research, practice, and policy.

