### Blinding

Those delivering interventions cannot be blinded to group allocation. Participants, assessors, and statisticians will be blinded throughout the entire trial period. Assessors are independent research assistants who are not involved in intervention delivery. Intervention providers are asked to not disclose group assignment to participants and assessors such as not talking about the mHealth intervention. Statisticians will receive data with unlabeled group coding and labels will only be revealed after completion of statistical analyses and start of interpretation of results.

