**Individual**		
Intervention	**·**Content: Providing medical consultation services and knowledge unrelated to healthy lifestyles (e.g., hospital treatment procedures) **·**Material: Homemade videos or weblinks to videos, and pictures **·**Provider: Group manager **·**Where: WeChat group **·**Schedule: For 6 months. Providing topics unrelated to healthy lifestyles twice a week	**Knowledge:** **·**Content: Providing medical consultation services and regular daily health knowledge related to healthy lifestyles and other topics (e.g., hospital treatment procedure) **·**Target: Changing misconceptions about healthy lifestyles; increasing knowledge about healthy lifestyles **·**Material: Homemade videos or weblinks to videos, and pictures **·**Provider: Group manager **·**Where: WeChat group **·**Schedule: For 6 months, providing topics related to healthy lifestyle once a day, and providing topics unrelated to healthy lifestyles twice a week **Skill:** **·**Content: One-on-one health coaching **·**Target: Guiding changes in unhealthy lifestyle; guiding engagement in healthy lifestyles; providing skills in maintaining healthy lifestyles **·**Materials: Live streaming platform, online course (e.g., exercise, diet), recipe (guided by the Mediterranean diet), tools (e.g., fitness aids such as elastic bands, medication aids) **·**Provider: Health professor, group manager **·**Where: WeChat and Tiktok live streaming platform, and homemade videos **·**Schedule: Being scheduled for 6 months. Live classes are offered twice a week; daily recipe and daily exercise guidance were provided
Self-management	None	**Empowerment:** **·**Content: Participants’ voluntarily online documentation of their daily lifestyle **·**Target: Self-management of health lifestyles with encouragement, self-supervision, and supervision from others **·**Materials: Gift (household goods) **·**Where: WeChat and offline activities **·**Provider: Group manager **·**Schedule: Inviting all participants document daily lifestyles (scheduled for 12 months) One-to-one online communication once a week to remind unhealthy lifestyle modification or healthy lifestyle maintenance (within 6 months). Being awarded with gifts consisting of daily necessities (e.g., soap and laundry detergent) for participants who document lifestyles well for that month in monthly offline activity (within 6 months)

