Self-management	None	**Empowerment** **·**Content: Medical consultation and peers’ encouragement **·**Target: Developing healthy lifestyle with the help of medical staff and peers who perform well in healthy lifestyles **·**Where: WeChat group, local medical centers **·**Provider: Group manager, doctors (from geriatric department, cardiovascular department, nutrition department, rehabilitation department of top three hospitals), local medical workers, and socially active peers **·**Schedule: Holding offline free medical consultations each quarter, giving advice on healthy lifestyles for participants. Sending gifts to participants who do well in online activities (once a month) and who have improved health status (once a quarter). Encouraging peers who perform well in healthy lifestyles to share their experiences of healthy lifestyle maintenance and encouraging other participants in offline activities, once a month

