#### Tools for intervention implementation

Intervention and control groups in each community will be assigned one trained group manager and one local medical doctor or nurse with at least 5 years professional experience. The 3SLIFE intervention will be implemented through online and offline activities. Online interventions will be delivered through WeChat and Tiktok Channels, two mainstream live streaming apps in China, to guide diet, exercise, and medication, etc. For online activities, group manager and local physicians will provide healthy lifestyle information and skills (e.g., exercise guidance, recipes) as well as self-management skills with the support of health tools (e.g., fitness aids such as elastic bands) in WeChat groups and one-on-one communication by WeChat or phone. Offline interventions will be guided by cognitive behavior therapy (CBT) [40] at local health centers through group managers, with group managers and physicians designing and recording related healthy lifestyle promotion activities. During the intervention, investigators will record participants' responses and satisfaction with the intervention and obtain their daily health records (e.g., photos of meal preparation following recommended recipes). For individuals with good adherence to the intervention or improved physical examination indicators, value-added gifts (e.g., household goods) will be released as rewards.

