### Data collection and outcomes

Questionnaires and scales will be administered in onsite face to face interviews at baseline, 3, 6, 9, and 12 months. Face to face interviews will be conducted by trained research assistants (students). Physical examinations will be conducted by community doctors with at least 5 years of clinical experience. Biological samples such as blood and stool samples will be collected by trained nurses and delivered to specialized laboratories with procedures to keep the cooling chain and avoid contamination.

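### The recall aid for the self-reported primary outcome appears to exist only in the intervention arm, and the article is inconsistent about who collects outcomes

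*Protocol article*

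**What the plan says.** **Recall aid.** The limitations paragraph of the Discussion accepts that the mainly questionnaire-based outcomes are open to recall and social-desirability bias. As a remedy it says that "for some indicators prone to recall bias, we will provide documentation records for participants to help recall their lifestyles". It names no arm.

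**Lifestyle documentation.** Table 1 (Individual, Self-management) lists "voluntarily online documentation of their daily lifestyle" in the intervention column, with the schedule "Inviting all participants document daily lifestyles (scheduled for 12 months". The control entry in that row is None.

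**Who assesses.**
- Blinding: "Assessors are independent research assistants who are not involved in intervention delivery". Participants and assessors are to stay blinded throughout.
- Data collection and outcomes: interviews are done by student research assistants, and "Physical examinations will be conducted by community doctors with at least 5 years of clinical experience".
- Confidentiality: questionnaires are the task of medical staff.
- Discussion: as a further safeguard for the questionnaire outcomes, "all group managers will receive standard investigation training". Group managers are named in Table 1 as providers of the intervention.
- Tools for intervention implementation: each community, in both arms, has a group manager and a local doctor or nurse.

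**Gifts.** Tools for intervention implementation provides rewards: "For individuals with good adherence to the intervention or improved physical examination indicators, value-added gifts". Table 1 (Community, intervention column) adds gifts for those "who have improved health status (once a quarter").

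**The concern.** A randomised comparison needs the outcome to be measured in the same way in both arms. Here the aid meant to reduce recall bias is, as far as the article shows, a by-product of the treatment. Applied as written, it can turn a recall error common to both arms into one that differs by arm.

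The primary outcome makes this matter more, because it is a change from baseline and baseline is collected before randomisation. Intervention participants would be compared unaided at baseline and aided at 6 months; controls would be unaided both times.

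A participant who arrives with twelve-month lifestyle records, or refers to them, also tells the interviewer which programme the village received.

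Intention-to-treat analysis, multiple imputation, reference-based imputation and the per-protocol analysis do not address a difference in measurement. The limitations paragraph admits the bias but not that it could differ by arm.

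**Working it through.** **1. Which components are exposed.** Table 2 gives the source of each component.
- Smoking and alcohol: questionnaire.
- Physical activity: International Physical Activity Questionnaire.
- Diet: food frequency questionnaire.
- Overweight/obesity: BMI from medical examination.

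Four of five are self-reported.

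**2. Which records exist at the assessments.** Documentation runs for 12 months, so in the intervention arm it covers the 3-, 6-, 9- and 12-month visits. The article describes no corresponding control record. There are two readings:
- Records in the intervention arm only: measurement differs by arm, and the blinding of the interviewer is at risk.
- Records in both arms: controls receive a self-monitoring element that Table 1 says they do not get.

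Neither reading leaves the Discussion, Table 1 and Blinding sections in agreement.

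**3. Who collects outcomes.** Blinding and Data collection name independent research assistants, who are students, for interviews. Confidentiality names medical staff for questionnaires. These differ on their face. The Discussion's training of group managers, offered as a safeguard for questionnaire data, only implies a role. For BMI, no sentence separates the examining community doctors from the local clinicians on the delivery teams.

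**4. The plan's own figure.** Inputs from Sample size: p1 = 0.02, p2 = 0.12, power 0.80, alpha 0.05 (taken as two-sided), attrition 20%. With the pooled chi-squared formula and mean rate 0.07:

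n = [1.960 × √(2 × 0.07 × 0.93) + 0.842 × √(0.02 × 0.98 + 0.12 × 0.88)]² / 0.10²

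n = [0.707 + 0.298]² / 0.01 ≈ 101.01, rounded up to 102 per group. Then 102 / 0.80 = 127.5, rounded up to 128. Both stated figures reproduce.

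**5. Illustration of scale.** The article gives no misreporting rate, so the counts here are assumptions. Take no true effect, 2 of 102 favourable in each arm, and add falsely favourable intervention participants. Clustering is ignored.

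| Added | Comparison | Pooled z | p |
|---|---|---|---|
| 5 | 2/102 vs 7/102 | 0.0490 / 0.0288 = 1.70 | 0.088 |
| 10 | 2/102 vs 12/102 | 0.0980 / 0.0354 = 2.77 | 0.006 |

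As a rate: if a fraction f of otherwise unfavourable intervention participants is misclassified, the apparent rate is 0.02 + 0.98f.

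| f | Apparent rate | Ratio to 2% | Chance of a significant result |
|---|---|---|---|
| 3% | 4.9% | 2.5 | 0.21 |
| 5% | 6.9% | 3.5 | 0.40 |
| 8% | 9.8% | 4.9 | 0.66 |
| 10.2% | 12.0% | 6.0 | 0.80 |

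The last row equals the planned effect by construction. The table shows only that, against a 2% control rate, a small number of reclassified people moves the result a long way.

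**The case against.** **The recall sentence names no arm.** It may mean something the study hands to everyone, and it does not say that interviewers see the records. The detailed assessment procedure sits in an operation manual that is not shown. This is fair, and it is why the one-arm reading is an inference from Table 1. It does not remove the need to reconcile the passages, because the alternative reading contradicts Table 1.

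**Deliverers are not shown to be assessors.** A reader might infer that group managers or delivering doctors measure outcomes and that the blinding claim is therefore false. The article does not support this. No sentence says so; assessors and group managers have separate training under Quality control and quality assurance; and the investigation training may concern ordinary contact with participants. Local clinicians are also assigned to both arms alike, so any overlap would be a question of assessor independence, not a procedural difference between arms. Only the inconsistency stands.

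**Gifts.** A reader might see them as paying for favourable answers. They are part of the treatment, and the improvement-based ones quoted above depend on health status or examination indicators, not on questionnaire replies. They do not in themselves contradict assessor blinding.

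**Direction and mechanism.** A diary could bring forgotten drinking or smoking back to mind and so work against the intervention. It is also not established that one changed answer makes a participant favourable: activity and diet are scored by quintiles of composite measures, and the binary cut-points are not given. Both objections stand.

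**Conclusion.** The point holds as a conflict between the Discussion, Table 1 and Blinding. As written, the recall aid either makes measurement of four of the five primary components differ by arm, with a risk of unmasking interviewers, or contradicts the control entry in Table 1. Favourable reporting is plausible, but the bias could go either way. Its size cannot be derived from the article, and the 10-of-102 figure is an illustration that rests on an assumed count and ignores clustering.

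The point about outcome collectors holds only as an inconsistency to be resolved. The article does not show that those who deliver the programme will assess it, nor that the gifts distort the questionnaire data. The stated sample size is unaffected.

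**What to change.** 1. State that intervention lifestyle records are neither used nor shown at outcome assessments, and that both arms answer the same questionnaire unaided. Amend the limitations sentence accordingly. Cost: slightly noisier recall, equal in both arms.
2. Reconcile Blinding, Data collection and outcomes, Confidentiality and the Discussion so that interviews are done only by the independent research assistants. Clarify or remove the mention of investigation training for group managers. Cost: wording.
3. Keep physical examinations with community doctors, but have BMI measured by doctors who do not deliver the programme in that village. Cost: some rearrangement of staff between villages.
4. Optionally, release improvement-based gifts only after that visit's data are recorded and locked. Cost: a short delay in handing them out.

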## Data Availability

All investigators and implementation staff will have unrestricted access to the full data set for verification interpretation purposes. Data will be made available to the public after publication of study findings upon request from the corresponding author ([name], [contact]; [name], [contact]).
